### Trial design

COPD-HIIT is a prospective, multi-centre, randomized, controlled, parallel-group superiority trial with the assessor and statistician blinding, featuring a 1:1 allocation ratio and two separate phases. In phase 1, we will investigate the effects and mechanisms of a 12-week intervention with supramaximal HIIT compared to MICT in people with COPD and matched healthy controls. Upon completion of the initial 12-week intervention and follow-up assessments, people with COPD, but not healthy controls, will enter phase 2 of the trial. Phase 2 comprises a 21-month maintenance exercise program. Subsequently, exercise training (supramaximal HIIT or MICT) will be performed until a 24-month follow-up. A separate control group of people with COPD, receiving usual care only, will undergo assessments at baseline and 24 months. As the usual care arm is not included in the randomization, phase 2 is a partially randomized controlled trial. See Fig. 1 and Fig. 2 for an overview of the COPD-HIIT project design.

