### Eligibility criteria

The inclusion criteria are as follows:60 years of age or olderIndependent in activities of daily livingFor people with COPD: post-bronchodilator spirometry confirmed COPD diagnosis (forced expiratory volume in one second (FEV_1_) to forced vital capacity (FVC) ratio < 0.70) [2].For people with COPD: symptomatic (COPD assessment test (CAT) ≥ 10 or modified Medical Research Council dyspnoea scale (mMRC) ≥ 2) or not being regularly physically active at a moderate or high intensity over the last year defined as not meeting WHO requirements for physical activity [46].For healthy controls: normal lung function

The exclusion criteria are as follows:

Movement-related, cardiovascular, neuromuscular, metabolic, skeletal and/or rheumatic conditions, and diseases that are unstable and/or prohibit exercise or tests, based on screening by a physician. For example, but not limited to:
Musculoskeletal pain prohibiting participation in physical tests and exerciseRecent myocardial infarction, coronary artery bypass grafting, angioplasty, or other cardiac eventsUncontrolled arterial hypertensionPathological ECG-findings during CPETOther lung conditions, including but not limited to uncontrolled or very severe asthma, interstitial lung disease, lung cancer, pulmonary hypertension, pulmonary vascular disease, and pulmonary fibrosis.

Medical conditions and treatments with known effects on brain function and cognition, for example:f)Previous trauma to the head with lasting cognitive or symptom-related issuesg)Physical or mental disabilitiesh)Neurological condition (dementia, multiple sclerosis, stroke)i)Psychiatric illness not including depression or general anxiety disorderj)Severe cognitive impairmentk)Recent or current cancer diagnosis and treatmentl)For those accepting MRI or PET/CT: metal implants, pacemakers, claustrophobia, and other MRI-incompatible factors.m)Inability to read or speak Swedish (Umeå participants), Dutch, French (Hasselt participants), or English (Umeå and Hasselt participants)

For people with COPD:n)Comorbid conditions that limit exercise performance to a greater extent than the COPD diagnosis.o)Currently participating in a pulmonary rehabilitation program or have been involved in pulmonary rehabilitation in the last 12 months.p)Experienced a COPD exacerbation that led to a change in medication dosage or frequency in the preceding 6 weeks.

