#### Passive control group: usual care

The passive control group will receive usual care alone and a standardized phone call (see additional file 4) every 3 months including assessment of symptoms of exacerbations. Health status (CAT) and disease-specific quality of life (CRQ) will be assessed by sending a letter with the questionnaires via the post for self-administration or by a phone call. We will match the participants in the usual care group to those randomized to HIIT or MICT by age, sex, disease severity (GOLD A/B/E), educational level, and physical activity.

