### Assessments only at baseline

Assessments only at baseline are measures with the purpose to characterize the participants and are only considered outcomes for cross-sectional comparisons between groups at baseline.Pulmonary function testing will be performed including spirometry, lung volumes, and diffusion capacity for carbon monoxide according to ATS/ERS guidelines [53–55]. At follow-up testing, a spirometry is performed for up-to-date pulmonary data during cycling tests.Anthropometrics: to measure height, participants will stand against a stadiometer without shoes. Body weight loss and malnutrition will be assessed using the Self-MNA® Mini Nutritional Assessment. The Self-MNA® consists of 5 questions related to food intake, weight loss, mobility, recent psychological stress or acute disease, neuropsychological features (dementia/sadness), and three anthropometric assessments (height, weight, and calf circumference), resulting in a calculated score (maximal 14 points). Based on the score, the participant is categorized as malnourished (0–7 points), at risk of malnutrition (8–11 points), and normal nutritional status (12–14 points). The Self-MNA® is the self-report version of the MNA short form that has been previously used in COPD [56], validated against the full MNA [57], and is advised to use as a nutritional screening tool by the European Society for Clinical Nutrition and Metabolism guidelines [58]. The administration of the Self-MNA® takes less than 5 min to complete.Information on smoking status and habits, pack years, exacerbations, and hospitalisations during the last 12 months, medical history, comorbidities, pharmacological treatments (any changes in medication will also be collected during the trial period), educational level, and history of risk factors for COPD (i.e., biomass exposure, occupational exposure, and host factors).Information on training status: any previous training experience, aerobic training experience, and specifically, exercise habits (type, frequency, intensity) in the last 12 months.The modified medical research council (mMRC) dyspnoea scale (0–4, arbitrary units) will be used to assess baseline dyspnoea [59]. The mMRC dyspnoea scale is used to evaluate the degree of baseline functional disability in patients with respiratory diseases [59]. The scale consists of five levels ranging from 0 to 4, each representing a different level of dyspnoea where grade 0 is the lowest degree of functional disability, and 4 the highest. The scale is easy and efficient to use and widely used in the COPD literature and is integrated with the Global Initiative for Chronic Obstructive Lung Disease (GOLD) clinical classification scheme [2]. The mMRC takes 2–3 min to complete.Physical activity (see description above).

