### Multicentre trial and covariates

The specific trial design is a stratified multicentre trial with individual randomization at each involved centre. Using this design results in a gain in power [126], not a loss in power typical of randomized cluster trials where observations on individuals in the same cluster tend to be correlated. Therefore, no increase in the sample size is necessary even though we collect data at two research centres. In contrast, the sample size could be reduced for a given power [126]. Furthermore, in the statistical analysis (described below), we will adjust the analysis for the predictive covariates age, sex, VO_2_peak, and centre—the latter as appropriate when stratifying the randomization. Adjusting for covariates in the statistical analysis is also associated with a gain in statistical power, or equivalently, a reduced sample size requirement [127–129]. Yet, we have taken a conservative approach and have not accounted for this when estimating the required sample size due to the complex assumptions the calculations require, leading to uncertainty of how much reduction in the required sample size can be expected.

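### The non-randomised usual-care arm is neither matched nor, in the stated model, adjusted for airflow limitation, although lung function is measured at baseline

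*Protocol article*

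**What the plan says.** The Trial design section is open about the status of the third arm: "As the usual care arm is not included in the randomization, phase 2 is a partially randomized controlled trial". The section on the passive control group then gives the matching rule. Four of the factors are age, sex, education and physical activity. The fifth is written as "disease severity (GOLD A/B/E", and this GOLD letter is the only disease factor in the list.

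Under Eligibility criteria, the lung function requirement for people with COPD is a "post-bronchodilator spirometry confirmed COPD diagnosis", defined by an FEV1/FVC ratio below 0.70. No lower or upper FEV1 limit is set. The second COPD criterion is "symptomatic (COPD assessment test (CAT) ≥ 10 or modified Medical Research Council dyspnoea scale (mMRC) ≥ 2) or not being regularly physically active", so symptoms are one of two routes into the trial.

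The section Assessments only at baseline provides for spirometry, lung volumes and diffusion capacity. It also describes mMRC as "integrated with the Global Initiative for Chronic Obstructive Lung Disease (GOLD) clinical classification scheme". The article does not otherwise define groups A, B and E.

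For the analysis, Multicentre trial and covariates lists the "predictive covariates age, sex, VO_2_peak, and centre". Statistical methods—outcomes adds the baseline value of each outcome and specifies one phase 2 model with all three arms.

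**The concern.** In phase 2, two of the three pairwise contrasts (HIIT versus usual care and MICT versus usual care) are not protected by randomisation. Their comparability depends on the matching list and the covariates. A prognostic variable in neither is balanced only indirectly.

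Airflow limitation appears to be such a variable. If usual care is recruited with more or less of it than the exercise arms, part of any difference in the 24-month course of fitness, muscle power or cognition could be credited to exercise. The same applies to exacerbations, hospitalisations and deaths. A larger sample does not reduce a bias of this kind, so the planned blinded sample size re-estimation gives no protection against it.

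**Working it through.** The plan states no figure on this point, so there is none to reproduce. The check has two parts.

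**1. Where lung function appears in the plan**

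- Entry: FEV1/FVC ratio only, with no FEV1 range (Eligibility criteria).
- Baseline measurement: yes (Assessments only at baseline; Table 5).
- Usual-care matching list: not named (Passive control group).
- Randomisation strata: sex and centre only (Allocation, randomization, and masking). These do not apply to usual care in any case.
- ANCOVA covariates: baseline value, age, sex, centre and VO2peak (Statistical methods—outcomes). Lung function is not named.
- Check that matching worked: stated for COPD against healthy controls (Statistical methods—additional analyses). No such check is stated for usual care against the exercise arms.

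Two people with COPD who share age, sex, education, activity level and GOLD letter therefore meet every matching criterion whatever their FEV1, provided that the letter does not itself encode FEV1. The article's remark on mMRC supports the symptom part of that reading. It does not show that exacerbation history is the other component, or that FEV1 is excluded. This remains an assumption.

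**2. How large the bias could be (illustration)**

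Formula: bias = D × r × SD.

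- D is the difference in mean FEV1 % predicted between usual care and an exercise arm, in SD units. Assumed: 0.25, 0.5 and 1.0. If the SD is about 20 points (also assumed), these are 5, 10 and 20 points.
- r is the correlation of FEV1 with the 24-month change. Assumed: 0.1 to 0.3.
- SD is the outcome SD from the sample size section, treated here as the SD of change: 0.4 z for cognition and 4.6 mL/kg/min for VO2. The target differences there are 0.27 z and 3.5 mL/kg/min.

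D and r are meant as what is left once the listed covariates are in the model. If they are read as raw values, the results are upper figures before any reduction by those covariates.

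Cognition:

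- D = 0.25: 0.25 × 0.1 × 0.4 = 0.01 to 0.25 × 0.3 × 0.4 = 0.03 z, which is 4 to 11% of 0.27.
- D = 0.5: 0.5 × 0.1 × 0.4 = 0.02 to 0.5 × 0.3 × 0.4 = 0.06 z, which is 7 to 22%.
- D = 1.0: 1.0 × 0.1 × 0.4 = 0.04 to 1.0 × 0.3 × 0.4 = 0.12 z, which is 15 to 44%.

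VO2peak, for D from 0.5 to 1.0:

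- 0.5 × 0.1 × 4.6 = 0.23 to 1.0 × 0.3 × 4.6 = 1.38 mL/kg/min, which is 0.23/3.5 = 7% to 1.38/3.5 = 39% of the target.

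The documents give no value for D or r and no direction. The range shows what the assumptions imply. It is not a forecast.

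**The case against.** The strongest reply is that matching on the GOLD letter is a legitimate choice. The protocol says in brackets which severity it means, and it never claims to match on airflow limitation. Its Introduction says that extrapulmonary manifestations affect clinical outcomes whatever the degree of lung impairment. Usual care is matched on five factors, and the model adjusts for the baseline value of each outcome and for VO2peak, which may absorb part of an FEV1 difference. Lung function will be presented as % predicted among the baseline variables, so an imbalance could be seen if those are tabulated by arm. Further model detail is deferred to the SAP.

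Much of this stands. It rules out calling the matching an error and limits how much bias should be expected. It does not supply direct control of airflow limitation. The covariate list is already stated in the article, and matching takes place at recruitment, so an SAP cannot repair it afterwards.

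A reader might also infer that the entry criteria already settle the GOLD letter, so that matching on it achieves little. The documents do not support this. Physical inactivity is an alternative route to entry, and the Screening procedure section provides for people without symptoms on mMRC or CAT. Exacerbations bar entry only if they changed medication in the preceding 6 weeks. On the assumed meaning of the letters, A, B and E all remain possible, and no expected mix is given. The letter keeps its matching value and should not be dropped.

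**Conclusion.** The point holds in a limited form. The matching list and the stated covariates leave airflow limitation uncontrolled in the two non-randomised phase 2 contrasts, although the measurement is available. This depends on the GOLD letter not carrying FEV1, which the article supports only in part.

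The illustrative bias runs from 4% of the cognitive target (a 0.25 SD gap with r = 0.1) to 44% (a 1 SD gap with r = 0.3). The upper end combines both extreme assumptions. It would be tempting to conclude that the arms will differ widely in lung function. Nothing in the documents shows that; an imbalance is possible, not established. The randomised HIIT versus MICT comparison is unaffected in both phases.

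This is a low-cost improvement to the plan, not a flaw that invalidates it.

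**What to change.** - Keep GOLD A/B/E in the matching.
- Add baseline post-bronchodilator FEV1 % predicted as a covariate in the phase 2 contrasts with usual care. Because one three-arm model is planned, this is one extra term in that model. It also covers usual-care participants already enrolled.
- Where feasible, add FEV1 % predicted in broad bands to the matching of usual-care participants still to be recruited. The Trial status section reports 51 participants enrolled at acceptance, against 138 + 70 = 208 planned over both centres. The article does not say how many of the 51 were in usual care.
- Report baseline balance of usual care against HIIT and MICT, including lung function, alongside the check already planned against healthy controls.

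The cost is protocol wording, one model term and somewhat harder matching. The matching cost is real, since only 46 usual-care participants are planned (30 in Umeå and 16 in Hasselt) and five matching factors already apply. For that reason the bands should be broad and the covariate should be the main safeguard. No new measurement is needed, as spirometry is already required for entry and at baseline.

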### Criteria for discontinuing the intervention or modifying allocated interventions

Criteria for discontinuing the intervention for a given trial participant are adverse events, severe injuries, or illness preventing to participate in the intervention or on participant request. In the case of discontinuation, trial participants will be retained in the trial whenever possible to enable follow-up data collection which can be extended up to a maximal of 2 weeks. Modifications of the allocated interventions are described below in the adherence section.

### Interventions—adherence

#### Phase 1

To promote adherence to the interventions during phase 1, efforts will be made to design the training sessions to be pleasant for participants. We strive for easy access to training facilities and adequately sized training groups in a comfortable setting using appropriate equipment with personal monitoring from experienced health care professionals, such as physiotherapists, exercise physiologists, or other health care professionals with equivalent expertise. The motivational principle of ‘visual cues and feedback’ will be used as the participant receives continuous visual supporting (additional file 4, Figure S4-S5) information during exercise on the tablet through the Kinomap exercise training application (Kinomap, Douai, Nord-Pas-de-Calais, France), and the motivational principle of ‘verbal cues and feedback’ given by the instructor will be used to facilitate the exercise sessions (as described under ‘Supervision’). The importance of adherence to the interventions will be informed before and during the trial. Trial participation will, if possibly, be planned to avoid breaks due to holidays and festive seasons.

Attendance to the intervention will be documented by the instructor conducting the training sessions at each centre. If a participant misses a training session without notice, an instructor will contact the participant by phone the same day. If needed due to missed sessions, the intervention period can be extended by up to 1 week, or if needed to reach a 75% attendance rate (22 sessions) up to 2 weeks, given that the participant agrees to the extension. Adherence to the prescribed exercise training (duration, intensity, RPM) will be documented by the instructor and via the Kinomap exercise training application.

#### Phase 2

To promote adherence to interventions during phase 2, the motivational principle of ‘preferred environments’ is used where participants with COPD will be able to select in which setting they wish to continue their exercise training, i.e., home-based, outpatient, or mixed setting. Furthermore, they can at any time during the 21-month maintenance period change between the different settings.

The individuals with COPD continuing in a home-based or mixed setting will receive a home visit at the start of phase 2 to deliver the necessary equipment and to receive instructions on how to perform the endurance and resistance training exercises at home. Since the endurance exercise is similar to phase 1—the primary focus of the instructions is on the resistance exercises, which are instructed orally and/or practically. Practical demonstration of at least one upper and one lower extremity exercise will always be performed. All participants will receive a training diary that is specific to their group allocation (supramaximal HIIT or MICT), [47] RPE 6–20 and [47] CR-10 rating scales, and elastic training bands. If a participant uses a bike at home, they will also be provided with a dedicated booklet on how to handle the bike and guidance on utilizing the Kinomap application. During office hours, the instructor will also be reachable to provide support over the phone if needed.

Additionally, the motivational principle of ‘visual cues and feedback’ (additional file 4, Figure S4-S5) will be used as the participant receive continuous visual supporting information during exercise through the Kinomap application (as described under ‘Interventions’), while the motivational principle of ‘verbal cues and feedback’ given by the instructor to facilitate the exercise sessions will only be applicable when the participant chooses the outpatient setting (as described under ‘Supervision’). The motivational principle of ‘visual cues’ will also be used for the resistance training via the use of images of all the exercises (as described in additional file 5. – Figure S1-S3). The participants will also receive a standardized follow-up call at the start of every 2-week period, including pre-determined questions on adherence to the exercise interventions (duration, intensity, RPM). The instructor will also be able to access the performed exercise training via the Kinomap exercise training application. The feedback given by the instructor can also be considered to be a motivational strategy using the principle of ‘verbal feedback’. The intervention period in phase 2 will not be extended to account for missed sessions in any of the settings.

### Relevant concomitant care permitted or prohibited during the trial

#### Phase 1

Participants are encouraged to continue with their regular everyday physical activity but are prohibited to participate in other organized training programs during the 12-week trial period.

#### Phase 2

Participants are encouraged to continue with their everyday physical activity and are allowed to enrol in a pulmonary rehabilitation (PR) program if that would be offered during the 24-month trial period. Participants are encouraged to discuss the uptake of a PR program with the trial team. For participants in the HIIT or MICT arm, the trial team will make sure the participant can still proceed with their allocated endurance (supramaximal HIIT or MICT) modality within the PR program (if the PR program is attended within NUS or ZOL). For participants in the passive control group, enrolment in a PR program cannot be denied and will not result in exclusion from the trial, but these participants will not be included in the per-protocol analysis.

## Methods: data collection, outcomes, and analysis

### Standardisation

Assessors will have previous experience or be trained in the included outcome assessments before commencing the trial. Protocols will be developed to standardize procedures. All tests will be performed using equipment that is available at each trial centre, which will be standardized to the greatest extent possible via standard operating procedures. Efforts will be made to ensure within-participant as well as between-participant outcome assessments are performed at the same time of day to minimize the effects of diurnal variations.

### Screening procedure

Eligibility screening will start with a telephone call (Umeå and Hasselt) or an in-person conversation (Hasselt) by a member of the research team to each participant to assess the inclusion and exclusion criteria. The responsible pulmonologist at each trial centre will, after consent, screen the medical record of the participant to assess eligibility. If the participant is eligible based on the screening, the participant will receive an accelerometer (DynaPort®, McRoberts BV, The Netherlands) to document his/her physical activity level. The participant will be instructed to wear the accelerometer on the lower back during seven consecutive days. The quantity of physical activity will be assessed using the mean number of steps per day and time spent in at least moderate-intensity physical activities. Accelerometer data consisting of ≥ 8 h/day wear time with ≥ 4 days of measurements will be considered valid [52]. In people with COPD, self-reported physical activity level measured by indicator questions from the National Board of Health and Welfare in Sweden will be used to determine eligibility when people with COPD are non-symptomatic based on mMRC dyspnoea scale or CAT. In controls, the physical activity data will be used to assess matching potential together with age and sex, and thus eligibility, and for baseline physical activity level determination. Next, the participants proceed to two–three weeks of baseline assessments where abnormal findings on examinations can lead to non-eligibility and thus exclusion.

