### Participants and recruitment

We will recruit participants with COPD via primary and specialist health care or advertisement. Matched healthy controls will be recruited via advertisement. All advertisements will have approval by the regional ethical board and will be disseminated via billboards, newspapers, local organization contacts, or targeted social media (e.g., Facebook). Each participant will receive financial compensation in an amount determined by the local centre and ethical board. If a participant would drop out, payments will be pro-rated based on the length of time stayed or the number of visits performed in the trial.

The planned distribution of participants per centre is as follows: in Umeå, approximately two-thirds (*n* = 138) of the participants will be recruited and in Hasselt the remaining third (*n* = 70) of participants. Subsequently, 92 individuals with COPD (HIIT: *n* = 31, MICT: *n* = 31, usual care: *n* = 30) and 46 HC (HIIT: *n* = 23, MICT: *n* = 23) are planned to be recruited in Umeå, while 46 individuals with COPD (HIIT: *n* = 15, MICT: *n* = 15, usual care: *n* = 16) and 24 HC (HIIT: *n* = 12, MICT: *n* = 12) are planned to be recruited in Hasselt. The enrolment period is expected to extend over approximately 24 months.

Written informed consent will be obtained by the assessors (AN, JJ, JDB, and DC) trained in Good Clinical Practice after all procedures have been explained, before the start of the trial during participants’ first test day.

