#### Statistical methods—outcomes

For primary and secondary outcomes with continuous data, treatment effect will be estimated by mean change-from-baseline (delta-value (Δ)) with 95% confidence intervals and the effect size (ES). The between-group effects will be analysed using analysis of covariance (ANCOVA). In the ANCOVA, baseline values, age, sex, centre, and VO_2_peak will be used as covariates. In phase 1, the primary analyses will be one model for the COPD group and one model for HC. In addition, to investigate any differential effects to the interventions between COPD and HC, a two-way ANCOVA including the Group (COPD/HC) × Intervention (supramaximal HIIT/MICT) interaction will be performed. In phase 2, there will be one model with the three arms (supramaximal HIIT, MICT, and usual care). Additional details will be provided in the SAP.

The assumptions of linearity, normality of residuals, and homogenous variance will be checked using residual plots, normal quantile plots, and histograms. Violations of linearity and normality assumptions will be dealt with by transformations of the dependent variable or non-linear modelling of the independent variables. Outliers will not be removed unless there is a methodological reason for it.

Feasibility of intervention outcomes and number of responders will be described with descriptive statistics and analysed with between group (HIIT/MICT) comparisons in both the COPD (phase 1 and 2) and HC group (phase 1).

In phase 1, hospitalization and exacerbations during the intervention will be presented descriptively. In phase 2, mortality, hospitalizations, and exacerbations will be presented with descriptive statistics and analysed using Kaplan–Meier curves and Cox proportional hazard models.

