#### Statistical methods—additional analyses

Pairwise comparisons between COPD and healthy controls will be conducted at baseline to investigate if matching has been successful, as well as to compare the cohorts using recommended methods for parametric and non-parametric data.

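### Education is neither a matching factor for healthy controls nor a stated covariate, which leaves chiefly the baseline COPD-versus-control comparison of cognition open to confounding

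*Protocol article*

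**What the plan says.** **Controls.** The protocol article, Participants and recruitment, states: "Matched healthy controls will be recruited via advertisement". People with COPD come through primary and specialist care or by advertisement. Under Screening procedure, the control matching factors are three: "In controls, the physical activity data will be used to assess matching potential together with age and sex, and thus eligibility".

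**Usual care.** This other non-randomised group, used in phase 2, is matched to the exercising COPD participants "by age, sex, disease severity (GOLD A/B/E), educational level, and physical activity".

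**Education as data.** Assessments only at baseline lists educational level among the information recorded to characterise participants.

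**Covariates.** Statistical methods—outcomes says: "In the ANCOVA, baseline values, age, sex, centre, and VO_2_peak will be used as covariates". Multicentre trial and covariates gives the same set without the baseline value: "we will adjust the analysis for the predictive covariates age, sex, VO_2_peak, and centre". Education is in neither list.

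**Comparisons.** Primary objective 1 sets the effects in COPD against those in matched healthy controls, with cognition as one of three primary outcomes. The analysis is laid out as follows: "In phase 1, the primary analyses will be one model for the COPD group and one model for HC". For differential response between cohorts, in addition, "a two-way ANCOVA including the Group (COPD/HC) × Intervention (supramaximal HIIT/MICT) interaction will be performed". At baseline, "Pairwise comparisons between COPD and healthy controls will be conducted at baseline to investigate if matching has been successful", and the same sentence also has the cohorts compared with each other, with no adjustment set named.

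**The concern.** Whether someone has COPD is not randomised. Any comparison of cognition between the cohorts therefore rests on matching and on adjustment, and education is missing from both. The protocol itself regards education as worth balancing: it is on the usual care list, and, unlike the GOLD group on that list, it applies to healthy people as well. The recruitment routes differ in part, which is one way for the cohorts to end up with different schooling.

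If they do, a baseline gap in the global cognitive score could be read as a COPD deficit when part of it reflects education. The baseline check of matching could reveal such a gap, but the article states no remedy for one. The Discussion presents the matched controls as a strength of the trial, so the comparison will carry weight in interpretation.

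**Working it through.** The plan gives no figure on this point, so there is nothing to reproduce. The check is which comparisons are exposed, then how far under stated assumptions.

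**1. Which comparisons are exposed**

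- HIIT versus MICT within COPD, and within controls: both are randomised, so education is balanced in expectation. Not exposed.
- Baseline COPD versus control: non-randomised, education neither matched nor adjusted. Exposed directly.
- Cohort difference in baseline-adjusted change: the baseline score carries most of the education effect, leaving a remainder because the score is measured with error.
- Group × Intervention interaction: exposed only if the HIIT-MICT difference itself varies with education.

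**2. Baseline comparison by hand**

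The inputs are assumptions, since the documents give none: an education gap between cohorts of 0.25 to 0.75 SD and an education-cognition correlation of 0.2 to 0.4.

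Spurious difference (in SD of the score) = gap × correlation

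- Low: 0.25 × 0.2 = 0.05 SD
- Middle: 0.5 × 0.3 = 0.15 SD
- High: 0.75 × 0.4 = 0.30 SD

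If the score's SD is 0.4, the value used in Sample size, these become 0.05 × 0.4 = 0.02 z, 0.15 × 0.4 = 0.06 z and 0.30 × 0.4 = 0.12 z.

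**3. Simulation of all three quantities**

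The simulation used 92 people with COPD and 70 controls, allocated 1:1 to HIIT and MICT, with no true COPD effect and ANCOVA on change adjusted for baseline. The assumptions were an education gap of 0.25, 0.5 or 0.8 SD (COPD lower), an education-cognition slope of 0.2 or 0.4, test reliability of 0.8, no direct effect of education on change, and effect modification by education of 0, 0.1 or 0.2 per SD. There were 600 runs per setting. Results are in SD of the score. The cohort difference in change is the one at MICT, because the model holds the interaction term.

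| Quantity | Education omitted | Education and education × intervention included |
|---|---|---|
| Baseline difference | −0.038 to −0.287 | −0.010 to 0.015 |
| Cohort difference in adjusted change | 0.005 to −0.068 | −0.006 to 0.010 |
| Interaction, no modification | −0.020 to 0.010 | −0.012 to 0.009 |
| Interaction, modification 0.1 or 0.2 | −0.022 to −0.154 | −0.015 to 0.014 |

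The last row agrees with the simple product gap × modification: 0.25 × 0.1 = 0.025 and 0.8 × 0.2 = 0.16. The third row and the right-hand column are zero within simulation error.

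**The case against.** **The primary analyses are safe.** A reader might infer that the cognitive primary outcome as a whole is confounded. The documents do not support that. The outcome metric is change from baseline, the phase 1 primary models are randomised contrasts within each cohort, and the two-way model is introduced as additional. This part of the objection stands in full and confines the point to the comparisons between cohorts.

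**The two matching lists are not a contradiction.** Usual care is an arm of the phase 2 treatment model, whereas healthy controls are not a treatment comparator. Different lists for different purposes are legitimate. The usual care list shows only that the authors regard education as relevant, and that is all it is used for here.

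**No education gap is documented.** That is so: neither its existence nor its direction can be read from the article, and the recruitment routes overlap because people with COPD also come by advertisement. The size is therefore conditional.

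**Comparison with 0.27.** A reader might set 0.30 SD beside the 0.27 z planning difference and conclude that the bias could exceed a relevant effect. The scales differ. The 0.27 is a difference in change on the z scale, planned with SD 0.4, so it equals 0.27 / 0.4 = 0.675 SD. The spurious figure concerns a baseline level. The two should not be compared directly.

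**The SAP may deal with it.** The article leaves further model detail to the SAP, and the SAP could add education. The covariate list is nevertheless given in the article, twice, without it, so the point is properly raised now.

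**Rematching is not free.** A reader might infer that control matching must be redone. Table 5 places demographic data at Visit 1, after matching eligibility is assessed at screening. The usual care section gives no education bands that could be reused. Enrolment is also under way: 51 participants at acceptance, of 138 + 70 = 208 planned. A new eligibility rule would select later controls differently from earlier ones. This stands, and the fix rests on adjustment instead.

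**Conclusion.** The point holds in limited form. Education is left out of both control matching and the stated covariates, so the non-randomised COPD-versus-control comparisons of cognition are open to confounding by it. The exposure is graded:

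- The baseline comparison carries most of it, about 0.05 to 0.30 SD under the assumed gap and correlation.
- The cohort difference in baseline-adjusted change carries little, up to about 0.07 SD in the simulation. That assumes education has no direct effect on 12-week change; if it had one, the exposure would be larger.
- The interaction carries none without effect modification, and about 0.02 to 0.15 SD with the modification assumed.

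Every size rests on assumed inputs. What the article itself establishes is the omission, not that a bias is present. The randomised HIIT-versus-MICT results within each cohort are not in question.

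**What to change.** In Statistical methods—outcomes, add educational level to the covariates of the two-way ANCOVA for the cognitive outcomes, and include an education × intervention term at least as a sensitivity analysis. The main-effect term alone would not remove bias in the interaction if education modifies the training effect. In Statistical methods—additional analyses, add a baseline COPD-versus-control comparison of cognition adjusted for educational level, reported beside the unadjusted one. The within-cohort primary models need no change.

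Optionally, for controls still to be enrolled, ask educational level at the screening call and monitor its balance against the COPD cohort, without making it an eligibility rule. Adjustment works best when the cohorts overlap in education, and monitoring would show early if they do not.

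The cost is one or two degrees of freedom if education enters as a single score (more if it enters as categories), using data already collected, plus one screening question if the optional step is taken.
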